### Secondary outcomes

2.4

The secondary outcomes in this study include the Gn dosage, duration of COH, endometrial thickness and pattern, LH, E2, P level on trigger day, numbers of retrieved oocytes, high-quality embryo rate, biochemical pregnancy rate, clinical pregnancy rate, implantation rate, ectopic pregnancy rate, early miscarriage rate, multiple pregnancy rate and incidence of moderate and severe OHSS. The high-quality embryo was defined as embryos with 7-10 cells of 2PN origin and blastomere fragments ≤20% on day 3 after fertilization (22). Biochemical pregnancy was defined as a serum level of β-hCG of more than 10 mIU per milliliter (27). Clinical pregnancy was determined when at least one gestational sac was observed on TVS. Early miscarriage was defined as pregnancy loss before 12 weeks of gestation.

### Sample size calculations

2.5

According to the previous literature review, no study has reported whether GH can improve the ongoing pregnancy rate of patients undergoing fresh embryo transfer with GnRH-ant protocol. Combined with the data of our center, the ongoing pregnancy rate of patients receiving fresh embryo transfer under GnRH-ant protocol was about 51.5%, and that of patients receiving depot GnRH-a protocol was about 69.7% (unpublished), while GH could increase the ongoing pregnancy rate by about 12%. The sample size was estimated using the chi-square test with α=0.05 and 1-β=0.8, then we need about 133 people per group, considering 10% shedding, about 147 people per group are needed.

Considering that this study is a pilot study designed to initially evaluate the feasibility, safety, efficacy, and range of variation of the GH intervention. Based on the above considerations, one-third to a quarter of the estimated sample size was selected for the pilot study, 40 patients are included in each group, and 120 patients would be expected to be recruited for this study.

### Statistical analysis

2.6

In this study, IBM SPSS Statistics V21.0 software would be used for data analysis. Measurement data would be expressed as mean ± standard error and count data would be expressed as rate (%). Kolmogorov-Smirnov would be used for the normality test and Levene would be used for the homogeneity of variance test. If the statistical data were consistent with normal distribution, analysis of variance and Kruskal-Wallis H were used to compare the differences in clinical outcomes among the three groups. Posthoc analysis would be performed by Bonferroni. The rates would be compared by the Chi-square test. If the statistical data did not conform to a normal distribution, a non-parametric Mann-Whitney U test would be used. Multivariate logistic regression analysis would be used to evaluate the effects of different treatments on the ongoing pregnancy rate, and adjustments were made according to the age, BMI, AFC, basal FSH level, and AMH level of patients. Bilateral p<0.05 would be defined as a significant difference.

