### Procedures

2.2

Patients who meet the above criteria will voluntarily decide whether to participate in this study. Informed consent would be signed by the designated doctor and the patient. A total of 120 infertile patients would be enrolled. The patients would be divided into the depot GnRH-a protocol group, GnRH-ant protocol control group, and GnRH-ant protocol plus GH intervention group at a ratio of 1:1:1 by block randomization design. Considering the open-label design of this study, both the attending nurse and the patient would be informed of the intervention method, while the embryologist and laboratory technician would be unaware of the intervention method. Participants’ baseline characteristics would be acquired from the hospital information database, including age, body mass index, primary infertility/secondary infertility; infertility duration; cause of infertility, history of fertility treatment; past medical history; history of drug allergy; vital signs; physical examination; urine hCG test; electrocardiogram; basal FSH, LH, E2, PRL, T, P, AMH, AFC; blood routine; urine routine; blood biochemistry; coagulation function; blood type; hepatitis B, syphilis, HIV examination, etc. will also be recorded.

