### Primary outcomes

2.3

The primary outcome is the ongoing pregnancy rate (OPR). OPR was defined as a clinical pregnancy until after 12 weeks of gestation.

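### Kruskal-Wallis H is attached to the normal branch, so non-normal continuous outcomes in this three-arm trial have no three-group test and no clear multiplicity adjustment

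*Protocol article*

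**What the plan says.** Section 2.6 (Statistical analysis) sets a decision rule for continuous data. Normality is checked by Kolmogorov-Smirnov and equality of variances by Levene. The rule then reads, in order:

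- Normal data, comparison of all three arms: "If the statistical data were consistent with normal distribution, analysis of variance and Kruskal-Wallis H were used to compare the differences in clinical outcomes".
- Follow-up: "Posthoc analysis would be performed by Bonferroni".
- A sentence assigning the chi-square test to rates.
- Non-normal data: "If the statistical data did not conform to a normal distribution, a non-parametric Mann-Whitney U test would be used".
- Threshold, at the end of the section: "Bilateral p<0.05 would be defined as a significant difference".

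The design has three arms, allocated "at a ratio of 1:1:1 by block randomization design" (section 2.2), and "40 patients are included in each group" (section 2.5). The outcomes to which the rule can apply are in section 2.4: "The secondary outcomes in this study include the Gn dosage, duration of COH, endometrial thickness and pattern, LH, E2, P level on trigger day", together with the number of oocytes retrieved. Section 2.3 fixes the primary endpoint: "The primary outcome is the ongoing pregnancy rate (OPR"). That is a binary outcome, which section 2.6 analyses by chi-square test and logistic regression.

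**The concern.** Kruskal-Wallis H is the rank-based counterpart of one-way ANOVA for three or more groups. Section 2.6 names it under the condition where it is not needed and omits it where it is. Two problems follow.

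First, the normal branch lists ANOVA and Kruskal-Wallis together without saying which decides. Second, the non-normal branch names only a two-sample test for a three-arm comparison. An analyst who follows the text literally runs no overall test on a skewed outcome. That analyst must also decide which pairs to compare and whether to adjust. The Bonferroni sentence stands before the Mann-Whitney sentence and is separated from it by the sentence on rates, so the text does not settle whether it applies.

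At stake is the false-positive rate for each continuous secondary outcome that goes down the non-normal branch, and the freedom to choose among readings after seeing the data.

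**Working it through.** The documents state no error rate for the continuous outcomes, so there is no planned figure to reproduce on this point. The sample-size calculation in section 2.5 concerns the pregnancy rate and plays no part here.

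**Inputs from the protocol article.** Three arms at 1:1:1 (2.2), 40 per arm (2.5), two-sided p<0.05 (2.6), Bonferroni for post hoc analysis (2.6).

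**Assumptions.** No true difference between arms, complete data on all 40 per arm, and continuous data drawn either from a lognormal distribution (SD 0.8 on the log scale) or from a normal distribution. The documents give no distribution for any outcome.

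**Step 1: upper reference.** Three arms give 3 pairs. If the three tests were independent, the chance of at least one false positive would be 1 − (1 − 0.05)³ = 1 − 0.8574 = 14.3%. The pairs share arms, so the true figure is lower and was simulated.

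**Step 2: Bonferroni threshold.** 0.05 / 3 = 0.0167 per pair.

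**Step 3: simulation.** 10,000 trials per distribution, 3 × 40 patients:

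| Reading of the rule, per outcome | Lognormal | Normal |
|---|---|---|
| Three Mann-Whitney tests, each at 0.05 | 11.7% | 11.7% |
| Three Mann-Whitney tests, each at 0.0167 | 4.2% | 4.0% |
| One Mann-Whitney test only (a single pair of arms) | 4.7% | 4.9% |
| Kruskal-Wallis H at 0.05 | 4.9% | 4.8% |
| Kruskal-Wallis H first, then pairs only if significant | 4.9% | 4.8% |

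A separate run of 4,000 trials with a log-scale SD of 0.6 gave 12.7% for three unadjusted Mann-Whitney tests and 5.2% for Kruskal-Wallis. The simulation standard errors for the unadjusted figure are √(0.117 × 0.883 / 10,000) = 0.3 points and √(0.127 × 0.873 / 4,000) = 0.5 points. The 1.0-point gap between the runs is compatible with simulation error. Agreement is expected: these tests use only ranks, so without ties and with no true difference the shape of the distribution does not affect their error rate.

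**Step 4: what the misplacement does alone.** Kruskal-Wallis on normal data rejects 4.8% of the time. Its presence in the normal branch makes the rule ambiguous but does not itself raise the error. The possible inflation comes from the non-normal branch, and only if all three pairs are tested without adjustment.

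**The case against.** The strongest defence is that this is a compressed sentence. The authors name the correct three-group rank test and probably meant ANOVA or Kruskal-Wallis for three groups and Mann-Whitney for two. Because Levene's test is named, one could also read Kruskal-Wallis as the fallback for unequal variances. The Bonferroni sentence carries no qualification and directly follows a sentence naming a rank test, so it may be meant to cover all pairwise work. On that reading the error is about 4%.

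Much of this stands, and it rules out several stronger readings that a reader might infer:

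- That the whole rule is reversed. It is not: ANOVA is where it belongs, and Mann-Whitney is a valid rank test for one pair of arms.
- That false positives are inflated as a matter of fact. This needs all three pairs to be tested and none adjusted. Section 2.6 states neither.
- That the plan breaches its own 5% family-wise limit. Section 2.6 gives a significance threshold and sets no family-wise rate.
- That the listed outcomes are known to be skewed. Nothing in the article shows it.
- That the trial's main result is at risk. The rule does not touch the primary outcome.

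The defence does not rescue the text. Neither charitable reading is written down. Even under the unequal-variance reading, the non-normal branch would still lack a three-group test. Nor is this a detail left to an analysis plan, because the article states a rule and the rule as stated is wrong.

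**Conclusion.** The point holds in a limited form. Section 2.6 misplaces Kruskal-Wallis H, gives no rule for choosing between it and ANOVA, leaves non-normal continuous outcomes without a three-group test, and does not make clear whether Bonferroni applies to them. The misplacement is plain from the text. The effect on error is conditional: between about 4% and about 12% per outcome, depending on which reading the analyst adopts, against about 5% with Kruskal-Wallis.

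These figures assume 40 analysed patients per arm, no true difference and negligible ties. They cover one outcome at a time, not the whole set of secondary outcomes. Gn dosage, COH duration, LH, E2, P and oocyte number are candidates for the non-normal branch by assumption only. The consequence is confined to continuous secondary outcomes of a study described as a pilot, and the primary analysis is unaffected. The text should be corrected.

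**What to change.** Rewrite the two test-selection sentences in section 2.6 to say:

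- Approximately normal continuous outcomes are compared across the three groups by one-way ANOVA, in the Welch version if Levene's test shows unequal variances.
- Non-normal continuous outcomes are compared across the three groups by Kruskal-Wallis H.
- Pairwise follow-up is Bonferroni-adjusted in both branches: t tests in the first, Mann-Whitney U or Dunn tests in the second.

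The cost is two sentences. All the tests are standard, and no additional patients or data are needed. The change should be made before outcome data are examined, so that the choice of reading cannot depend on the results.

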##### Depot GnRH-a protocol group

2.2.1.1

The patient would be given a subcutaneous injection of 3.75mg leuprorelin (Biote Pharmaceutical, Beijing, China) or 3.75mg triptorelin (Dophereline^®^, Ipsen, France/Decapeptyl^®^, Ferring, Switzerland) after endometrial thickness was determined to be <5mm with no follicle growth by transvaginal ultrasonography (TVS) on day 2 of the previous menstrual cycle. Approximately 28 days after injection, the patient would be confirmed to have reached the pituitary down-regulation position (E2 ≤30pg/ml and LH ≤2IU/L). Recombinant follicle-stimulating hormone (rFSH, Genescience Pharmaceutical, Changchun, China) would be selected for COH. The initial dose would be selected by the attending doctor according to the patient’s age, BMI, and ovarian reserve, and the dosage would be 150-225IU per day. During COH, doctors are allowed to adjust the dosage of Gn according to the patient’s ovarian response, and the maximum daily dosage would not exceed 450IU. When patients have a slow ovarian response during COH, human menopausal gonadotropin (HMG) (Lizon Pharmaceutical, Zhuhai, China) is allowed, and the dosage is determined by the attending doctor. During COH, any other adjuvant drugs are not allowed. When patients have two dominant follicles ≥18mm or three follicles ≥17mm in diameter, they would be triggered with recombinant human chorionic gonadotropin (rhCG, Ovidrel^®^, Merck Serono, Germany).

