#### Follow-up plan

2.2.5

Patients would be followed on enrollment day, trigger day, ET day, 7 days after OPU, 15 days after ET, 28 days after ET, and 12 weeks of gestation (**Table 3**).

**Table 3 T3:** Overview of follow-up during the study.

Time	Follow-up Information
• Enrollment day	Patient randomization, collection of baseline characteristics of the participants (age, body mass index, primary infertility/secondary infertility; infertility duration; cause of infertility, history of fertility treatment; past medical history; history of drug allergy; vital signs; physical examination; urine hCG test; electrocardiogram; basal FSH, LH, E2, PRL, T, P, AMH, AFC; blood routine; urine routine; blood biochemistry; coagulation function; blood type; hepatitis B, syphilis, HIV examination, etc.).
• Trigger day	LH, E2, P levels; TVS; GH medication records; rFSH medication record; GnRH-ant medication record; HMG medication record; rhCG or GnRH-a medication record; untoward reaction record.
• ET day	Oocytes status; embryo status; luteal support medication record; number and morphological evaluation of transferred embryos; untoward reaction record.
• 7 days after OPU	Blastocysts status, collection of endometrium samples; untoward reaction record.
• 15 days after ET	serum β-hCG levels; luteal support medication record; untoward reaction record.
• 28 days after ET	TVS; luteal support medication record; untoward reaction record.
• 12 weeks of gestation	Pregnancy outcomes (ongoing pregnancy rate or early miscarriage or ectopic pregnancy); untoward reaction record.

hCG, human chorionic gonadotropin; FSH, follicle stimulating hormone; LH, luteinizing hormone; E2, estradiol; PRL, prolactin; T, testosterone; P, progesterone; AMH, anti-mullerian hormone; AFC, antral follicle count; HIV, human immunodeficiency virus; TVS, transvaginal sonography; GH, growth hormone; HMG, human menopausal gonadotropin; OPU, oocytes pick-up; ET, embryo transfer.

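### Section 2.6 analyses the continuous secondary outcomes without covariates, although the five covariates named for ongoing pregnancy are collected on everyone: possible lost efficiency at 40 per arm, not bias

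*Protocol article*

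**What the plan says.** Section 2.6 (Statistical analysis) sets the tests for continuous outcomes: "analysis of variance and Kruskal-Wallis H were used to compare the differences in clinical outcomes among the three groups", Bonferroni for the post hoc comparisons, and Mann-Whitney U where normality fails. No covariate is attached to any of them.

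The one adjusted analysis in 2.6 is a logistic regression for ongoing pregnancy, in which "adjustments were made according to the age, BMI, AFC, basal FSH level, and AMH level of patients".

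Section 2.4 lists the outcomes affected: "The secondary outcomes in this study include the Gn dosage, duration of COH, endometrial thickness and pattern, LH, E2, P level on trigger day", followed by the number of oocytes retrieved.

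Two other places bear on the point. Table 3 (section 2.2.5) puts the ovarian-reserve covariates in the enrolment-day data, "basal FSH, LH, E2, PRL, T, P, AMH, AFC; blood routine", together with age and BMI. Section 2.2.1.1 says that "The initial dose would be selected by the attending doctor according to the patient’s age, BMI, and ovarian reserve". Section 2.2.1.2 applies the same gonadotropin selection to the antagonist control group, and section 2.2.1.3 builds the GH arm on that group.

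**The concern.** Gn dosage starts from a dose chosen by age, BMI and ovarian reserve. Part of its variation between women should therefore be predictable from data that the trial already holds. A test without covariates leaves that part in the error term. The same may be true of oocyte number and, less certainly, of the other continuous outcomes.

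The stake is precision. Section 2.5 calls the trial a pilot meant to look at, among other things, efficacy and the range of variation, with 40 women per arm. For the binary primary outcome, 40 per arm gives only about 19% power for 51.5% against 63.5%. Much of what the pilot can say about GH will therefore come from the continuous outcomes, and intervals wider than the data require would weaken it.

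**Working it through.** **The plan's own figure.** The article's only power calculation concerns ongoing pregnancy: "The sample size was estimated using the chi-square test with α=0.05 and 1-β=0.8". The inputs are 51.5% (antagonist), 69.7% (depot agonist) and 51.5 + 12 = 63.5% (antagonist plus GH, reading the 12% as absolute).

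- Mean rate: 0.6157. Sum of squared deviations: 0.01712.
- Noncentrality at n = 133 per group: 133 × 0.01712 / (0.6157 × 0.3843) = 9.62. On 2 df at 0.05 this gives 79.95% power; 134 per group passes 80%.

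The stated 133 is therefore reproduced as a three-group chi-square. The article gives no such figure for a continuous outcome, and no SD or correlation.

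**Inputs for the check.**

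- From the article: 40 per arm, three arms, N = 120 (2.5); two-sided 0.05 (2.6: "Bilateral p<0.05 would be defined as a significant difference"); Bonferroni post hoc, taken as 0.05/3 = 0.0167 for each of three pairs; k = 5 covariates (2.6).
- Assumed: rho, the combined correlation of the five covariates with the outcome, from 0 to 0.6. Also assumed are full follow-up, one pooled error variance and common slopes across arms.

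**Formulas.** For a pairwise contrast with error pooled over the arms:

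- Unadjusted: df = 120 − 3 = 117; noncentrality = d / √(2/40), with d in SD units.
- Adjusted: df = 117 − 5 = 112; the variance is multiplied by V = (1 − rho²) × (1 + 5/111). The second factor, 1.045, is the cost of estimating five slopes.
- Power comes from the noncentral t distribution.

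**Results.** The difference with 80% unadjusted power at 0.05 is d = 0.632 SD. The same d has 65.4% power at 0.05/3.

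| Assumed rho | V | SE ratio √V | Power at 0.05 (unadjusted 80.0%) | Power at 0.05/3 (unadjusted 65.4%) |
|---|---|---|---|---|
| 0 | 1.045 | 1.022 | 78.2% | 63.1% |
| 0.2 | 1.003 | 1.002 | 79.8% | 65.2% |
| 0.3 | 0.951 | 0.975 | 81.9% | 67.9% |
| 0.4 | 0.878 | 0.937 | 84.8% | 72.0% |
| 0.5 | 0.784 | 0.885 | 88.6% | 77.5% |
| 0.6 | 0.669 | 0.818 | 92.8% | 84.5% |

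- **Interval width at rho 0.5:** √(0.75 × 1.045) = 0.885, so intervals narrow by about 11.5%. Using √0.75 = 0.866 alone would overstate this at 13%, because it ignores the cost of the five slopes.
- **Break-even:** V = 1 when rho² = 1 − 1/1.045 = 0.043, so rho is about 0.21. Below that, adjustment loses a little.
- **Worst case (rho = 0):** a loss of 1.8 points at 0.05 and 2.3 points at 0.05/3.

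**The case against.** A reader might infer that the unadjusted tests bias the GH effect, since randomisation is described only as blocked and a chance imbalance in AFC or AMH would pass into the estimate. The documents do not support that. Under randomisation such imbalance is already reflected in the standard error. It is the same efficiency argument in other words.

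A reader might also infer that precision is certainly being lost on every continuous outcome. That goes too far as well:

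- The size rests wholly on an assumed rho. At 0.3 the gain is about 2 points.
- Section 2.1 restricts the covariates themselves: age 20-35, BMI 18.5-25, basal FSH below 10, and AFC 7-15 or AMH 1.1-4.0. Restricted range tends to lower rho, although the "or" lets one of the last two vary more widely.
- The documented link is to the starting dose, within 150-225 IU. Dose may then be changed by response and HMG may be added, so total Gn dosage is only partly tied to the covariates. For COH duration, oocyte number, endometrial thickness and the trigger-day hormones, the article states no link.
- Basal LH, E2 and P may predict little on trigger day, after down-regulation in one arm and daily antagonist in the other two.

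All of this stands and limits the point. What does not stand is that the matter is merely left to an unseen analysis plan: 2.6 itself fixes both the tests and the scope of adjustment. Nor does the Bonferroni rule shrink the gain, which at rho 0.5 is about 12 points at 0.05/3 against about 9 at 0.05.

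**Conclusion.** The point holds as one of efficiency on secondary outcomes. Section 2.6 uses five covariates for ongoing pregnancy and none for the continuous outcomes, although all five are to hand. The planned tests are valid and no primary conclusion changes.

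The gain is about 2 to 9 power points at two-sided 0.05 for rho from 0.3 to 0.5, from a starting power of 80%. It is about 3 to 12 points at the Bonferroni level. The downside is about 2 points if the covariates predict nothing. These figures rest on the assumed rho and on ANOVA as the comparator; the gain over the rank tests that would apply to non-normal data was not computed. The case is best supported for Gn dosage. For oocyte number it is a reasonable expectation, and for the remaining outcomes it is open.

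**What to change.** In 2.6, before analysis, state that Gn dosage, number of oocytes retrieved, COH duration, endometrial thickness and trigger-day LH, E2 and P will be analysed by a linear model. Gn dosage and oocyte number have priority.

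- **Terms:** treatment arm plus age, BMI, AFC, basal FSH and AMH, the set already named for ongoing pregnancy. Adjustment for the basal value of the same hormone is optional.
- **Skewed outcomes:** log scale, or a count model for oocytes, so that a departure from normality does not force a return to a test without covariates.
- **Reporting:** the adjusted GnRH-ant plus GH minus GnRH-ant difference with its 95% CI. Keep the Bonferroni rule for pairwise tests.
- **Sensitivity analysis:** the unadjusted comparison now in 2.6.

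The cost is wording only: no new data, visits or patients. Five of 117 error degrees of freedom are spent.

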#### Oocytes pick-up and embryo transfer

2.2.2

Oocytes would be picked up 36-38 hours after the trigger. During the OPU, follicular fluid from dominant follicles (diameter ≥18mm, oocytes visible under microscopy) that are not contaminated by blood would be collected, centrifuged, and stored in a -80°C refrigerator. The remaining follicular fluid and follicular flushing fluid would be collected in 50ml centrifuge tubes, and granulosa cells would be separated and extracted by enzymolysis method, and stored at -80°C in the refrigerator. 16-18 hours after insemination, the embryonic pronucleus (PN) would be observed. The embryos would be observed on day 3 after insemination. High-quality embryos were defined as 7-10 cell stage embryos of 2PN origin with blastomere fragments ≤20% at day 3 after fertilization (22). For patients meeting the criteria of fresh embryo transfer, one day 3 high-quality embryo would be transferred, and all remaining embryos would be cultured to blastocyst stage and frozen. For patients who need to cancel fresh embryo transfer due to various reasons (**Table 2**), 0-1 day 3 high-quality embryos would be frozen according to the embryo condition, and the remaining embryos would be cultured to the blastocyst stage and frozen.

**Table 2 T2:** Reasons for canceling fresh embryo transfer.

Reasons	details
• High risks of OHSS	1. E2≥5000pg/ml or ≥18 follicles (GnRH-a trigger) on the trigger day; 2. E2≥1500pg/ml; 3. ≥18 oocytes obtained; 4. 1000pg/ml≤E2 ≤ 1500pg/ml on the day after OPU but the patient had mild OHSS symptoms.
• Endometrial and fallopian tube factors	1. Hydrosalpinx and intrauterine effusion occurred during COH; 2. Endometrial thickness ≤6mm on ET day; 3. Single endometrial polyps >10mm or multiple endometrial polyps (regardless of size);
• High progesterone level	1. blood progesterone level ≥1.5ng/ml on the trigger day; 2. blood progesterone level ≥1ng/ml for three consecutive days during the COH.
• Embryo factor	No high-quality day 3 embryos for transfer
• Patients’ factor	Patients request cancellation of fresh embryo transfer

OHSS, ovarian hyperstimulation syndrome; E2, estradiol; OPU, oocytes pick-up; COH, controlled ovarian hyperstimulation.

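### Chi-square for every rate implies pooling correlated embryos from the same woman in the high-quality embryo rate; sparse secondary outcomes also need an exact test

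*Protocol article*

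**What the plan says.** Section 2.6 (Statistical analysis) states that "count data would be expressed as rate" and then that "The rates would be compared by the Chi-square test". It gives no exception for clustered or sparse data. Logistic regression is named only for the ongoing pregnancy rate.

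Section 2.4 (Secondary outcomes) lists, among others, "numbers of retrieved oocytes, high-quality embryo rate, biochemical pregnancy rate" and "ectopic pregnancy rate, early miscarriage rate, multiple pregnancy rate and incidence of moderate and severe OHSS".

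Section 2.2.2 (Oocytes pick-up and embryo transfer) sets the quality criterion for the individual embryo: "High-quality embryos were defined as 7-10 cell stage embryos of 2PN origin with blastomere fragments ≤20% at day 3 after fertilization". It also shows that a woman can have more than one embryo, since in a fresh transfer "one day 3 high-quality embryo would be transferred, and all remaining embryos would be cultured to blastocyst stage and frozen".

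Section 2.2 randomises patients 1:1:1, and section 2.5 puts 40 in each group. The article gives no mean number of embryos per woman, no within-woman correlation, no denominator for the high-quality embryo rate, and no expected frequency for ectopic pregnancy, multiple pregnancy or OHSS.

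**The concern.** The unit randomised is the woman, but the high-quality embryo rate is naturally a count of embryos over a count of embryos. Embryos from one woman share her oocytes, the sperm source and the stimulation cycle, so their quality is likely to be positively correlated. A chi-square test on pooled embryos takes the number of embryos as the sample size. It then understates the variance and finds differences between arms too often.

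The outcome has some weight. The introduction cites improved oocyte quality among the effects of GH, and a spurious difference in embryo quality would colour the reading of any difference in pregnancy rates.

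A smaller concern is that the same rule covers outcomes that may produce only a handful of events. There the chi-square approximation can give a misleading p-value for the table actually observed.

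**Working it through.** No figure stated in the article is in dispute. The check asks what the stated rule does under plausible inputs.

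**Embryo rate**

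Inputs from the article: three arms, 40 women per arm, two-sided 5% level. Assumed, because the article gives neither: m = 4 to 8 graded embryos per woman, and within-woman correlation (ICC) 0.05 to 0.3.

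Design effect: DE = 1 + (m − 1) × ICC.

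The three-arm chi-square has 2 degrees of freedom and critical value 5.991. With clustering the statistic is inflated by about DE, so the true level is P(χ²₂ > 5.991/DE) = exp(−2.9955/DE).

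| m | ICC 0.05 | ICC 0.1 | ICC 0.2 | ICC 0.3 |
|---|---|---|---|---|
| 4 | DE 1.15, 7.4% | DE 1.30, 10.0% | DE 1.60, 15.4% | DE 1.90, 20.7% |
| 6 | DE 1.25, 9.1% | DE 1.50, 13.6% | DE 2.00, 22.4% | DE 2.50, 30.2% |
| 8 | DE 1.35, 10.9% | DE 1.70, 17.2% | DE 2.40, 28.7% | DE 3.10, 38.0% |

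Worked example for m = 6, ICC 0.1: DE = 1 + 5 × 0.1 = 1.5; exp(−2.9955/1.5) = exp(−1.997) = 0.136.

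Unequal embryo numbers raise the error rate. In a beta-binomial simulation (40 women per arm, mean of 6 embryos varying between women, assumed rate 0.4, 20,000 runs), the three-arm error rate was 10.7%, 16.8% and 28.5% at ICC 0.05, 0.10 and 0.20. The formula gives 9.1%, 13.6% and 22.4%. At ICC 0 the rate is about 5%.

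**Sparse outcomes**

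With 40 per arm, the expected event count falls below 5 when the event rate is under 5/40 = 12.5%.

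Example: three events, all in one arm (3/0/0 of 40 each). The pooled rate is 3/120 = 0.025, so 1 event is expected per arm. X² = (2² + 1² + 1²)/(1 × 0.975) = 6.15, p = 0.046. Exact p = 3 × C(40,3)/C(120,3) = 3 × 9,880/280,840 = 0.106. The two tests fall on opposite sides of 0.05.

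Averaged over all possible tables the picture differs. At assumed event rates of 1%, 2% and 5% with 40 per arm, the enumerated true size of the nominal 5% three-arm chi-square is 1.01%, 2.85% and 3.75%. For two arms it is 0.09%, 0.74% and 4.34%. At an assumed 10% it is 4.46% for three arms and 5.86% for two.

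**Primary outcome**

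Ongoing pregnancy is one result per woman. At the 51.5% and 69.7% quoted in section 2.5, 40 women give 20.6 and 27.9 expected pregnancies, with 19.4 and 12.1 non-pregnancies. Chi-square is adequate there.

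**The case against.** The strongest objection is that the article never states the unit of analysis. If the rate is one proportion per woman, it is a measurement and falls under section 2.6's rule for continuous data (analysis of variance or a rank test), and the clustering problem disappears. This stands as a limit on the finding. It does not remove the finding, because the outcome is named a rate and section 2.6 sends rates to chi-square, which cannot be run on per-woman proportions.

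The inflation also rests on assumed embryo numbers and correlations. That is so, and only the range can be given; but any positive correlation pushes the error above 5%.

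A condensed article may leave such detail to a fuller plan. That would answer a complaint about an omission. Here the article states an affirmative rule with no exception.

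Three stronger readings are tempting, and the documents do not support them:

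- A reader might infer that chi-square will produce too many false safety signals for rare events. The enumeration shows a three-arm error rate below 5%. Moreover, in the 3/0/0 example, the pairwise comparison of 3/40 with 0/40 gives p = 0.078 even by chi-square. A pairwise 0 v 4 (chi-square p = 0.040, exact 0.116) would miss 0.05/3 = 0.017 if the Bonferroni step in section 2.6 covers rates.
- A reader might take all the listed complications as certain to be sparse. The article gives no rates. Only multiple pregnancy can be expected to be sparse from the text, because one embryo is transferred.
- A reader might treat embryo quality as the trial's main mechanistic outcome. The mechanism the article sets out to study is endometrial receptivity (sections 2.2.3, 2.2.4 and 3). The embryo rate is one unranked item in a long secondary list of a pilot study.

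**Conclusion.** The point holds for the high-quality embryo rate. As written, the rule implies a test that ignores clustering by woman. Its three-arm error rate is about 7% to 38% in place of 5%, assuming 4 to 8 embryos per woman and a within-woman correlation of 0.05 to 0.3, and somewhat more when embryo numbers vary. It rests on reading the rate as pooled over embryos, which the rule implies but the article does not say. On either reading the text needs a change: a clustered analysis, or a stated per-woman unit with a test other than chi-square.

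For sparse outcomes the point is minor. The p-value of an individual table can be unreliable, but the planned test does not call too many differences significant on average.

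The primary outcome is not touched. Nor is the implantation rate after single-embryo transfer, where each woman contributes one embryo.

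**What to change.** In section 2.6, limit the chi-square rule to outcomes with one result per woman and add two sentences.

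1. State the denominator and unit of the high-quality embryo rate, and analyse it with the woman as cluster, by logistic GEE or a mixed model. Alternatively, compute one proportion per woman and compare these between arms with the methods already named for continuous data. Say how women with no embryos to grade are handled.
2. When expected counts are small (below 5 is the usual convention), use the Fisher or Fisher-Freeman-Halton exact test. Report exact confidence intervals for multiple pregnancy, ectopic pregnancy and moderate or severe OHSS.

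Recruitment, treatment and data collection do not change, and SPSS 21 runs GEE. The cost is less favourable reported precision for the embryo rate: over the assumed range the standard error grows by a factor of √1.15 = 1.07 to √3.1 = 1.76. The exact test is also more conservative than chi-square for rare safety outcomes, so the confidence intervals should carry the message there rather than the p-value.
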